### Ethics

No serious or lasting side effects have ever been reported in infants following the types of treatment used in this trial and no compensations claims have ever been made for this this age group in Denmark [35]. Because there is no experimental treatment involved, but only treatments, which are usually performed in clinical practice, no interim analyses are made and therefore no data monitoring committee is needed. Furthermore, no standardized treatment in the area exists that the child is withdrawn from.

All parents have given written informed consent for their child to participate in the study and for collection of information from hospital files (Additional file 4). Participation in this study is voluntary, and the parents can withdraw their child from the study at any time with no negative consequences for the child. Parents are advised to immediately contact the chiropractor (who can contact the PI if relevant) if they suspect any serious adverse effect during the project period. In any case of discontinuation, the child’s allocation group will be revealed for the parents. All cases of discontinuations/withdrawals will be registered with reason for withdrawal.

The study has been approved by The Regional Committee on Health Research Ethics (S-2015001), and data are being handled by a data manager at NIKKB according to regulations by the Danish Data Protection Agency. The Regional Committee on Health Research Ethics reviews an annual safety report and any amendments made in the protocol or the documents used in the trial.

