**Fig. 1 Fig1:**
[figure not shown]
Study flow chart and time lime for participants

#### Visit 1

At the first visit, the PI, who is a medical doctor, assesses the child for eligibility and provides oral and written information (Additional file 2) regarding the project.

At the first visit the PI furthermore completes an interview-based questionnaire (Additional file 3) with the purpose to collect information about baseline variables and potential clinical predictors and confounders. The choice of variables was based on knowledge from existing literature [6–8, 19–21, 23, 27, 32] and focus group discussions with chiropractors and health visitors. Questions concerns the child’s crying pattern, birth weight and length, current weight and length, feeding mode and pattern, burps, regurgitation, bowel movements, anamnestic and objective signs of musculoskeletal problems (e.g. favorite side), previous treatment of the colic or other condition/disease, the mother’s health and use of medication, the parents’ level of serious mental stress during pregnancy and after the birth, mental stress of the parents in everyday life, educational level and cohabitation status of the parents, smoking status of the parents, siblings with history of colic, the parents’ belief regarding the effect of chiropractic treatment on colic, and selected factors related to pregnancy and birth. With consent of the parents pregnancy and birth related factors will also be collected in the mother’s hospital record, e.g. mother diagnosed with depression, gestational age at birth, durations of the different stages in birth, abnormal presentation in the birth canal and interventions in birth.

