### Randomization and blinding

The allocation occurs through a 1:1 ratio by a predetermined restricted randomization scheme. The participants are stratified according to their age at enrollment (2–6 weeks; 7–10 weeks; 11–14 weeks) and the treating chiropractor. The eligible participants are randomly assigned in blocks of 4 to 6, according to computer-generated random numbers, to be enrolled in either the intervention or control group.

The computer generated block randomization was administered by a research assistant, not otherwise involved in the outcome measurements or the intervention. The research assistant then wrote the consecutive letters A and B on separate pieces of paper and then placed them in sealed opaque envelopes, which were given to each chiropractor. To take the above mentioned stratification into account the procedure was repeated and a different list of group allocation was made for each age level and each chiropractor in the study. When a child is randomized and an appointment booked, the PI informs the clinic of the next randomization number for that specific chiropractor and age group (which is a coded number not revealing group allocation). Only the chiropractor has the list that reveals if that certain randomization number means allocation to intervention or control group.

Hence, the intervention in this trial makes blinding of care providers impossible. The parents are blinded to their child’s allocation group during the project period. To uphold blinding of the randomization, all parents leave the chiropractor’s consultation room for a few minutes after history taking and examination, while the treatment is (or is not) carried out. For the analyses, the coding of intervention and control groups will be concealed from the PI and the statisticians performing the analyses. The randomization code will not be broken until the analyses are completed.

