### Outcome measures

The primary outcome measure is change in daily hours of crying (inconsolable crying and the time the child needs to be held and rocked to limit crying) based on the parental diaries (before and after treatment).

Secondary outcomes are based on information from parental diaries and the final questionnaire filled out by the parents and will include:Sleeping hours per day (change in mean daily hours of sleeping before and after treatment)Awake and content (change in mean daily hours of an awake and content baby before and after treatment)General Perceived Effect (colic has stopped/decreased/unchanged/increased)Bowel movements (more often/more rarely; easier/more difficult)Burps (easier/more difficult)Regurgitation (more/less)

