The study will contribute to establish the effect of chiropractic treatment on infantile colic in an area where limited evidence exists [27]. An increasing number of infants are treated in chiropractic clinics, and the results of the study will be highly relevant for all new parents seeking chiropractic care for their child’s colic. Furthermore, the results will support healthcare professionals in guidance of parents on an evidence based level, which does not exist today. Since associations between infantile colic and both short and long-term consequences for the child and family have been shown [6–8], proper treatment at an early stage might actually present as primary prevention of these disorders. Therefore, a potential positive effect of chiropractic treatment on infantile colic may benefit both individuals and society considerably. Furthermore, serious side effects of chiropractic care in infants have not been reported, and therefore a potential beneficial effect is likely to exceed potential risks [29, 35].

Infantile colic appear to have a multifactorial etiology and it may be unlikely to find one treatment that will fit all [24, 25, 27]. Therefore there is a need to explore if certain subgroups will benefit more from a specific treatment. If confirmed, this could indicate a causal relation and form the basis for a more stratified care that does not exist today.

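### The only adverse-event route the article describes leaves notification of the PI to the unblinded treating chiropractor's discretion, so harms may be under-recorded, and unequally by arm

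*Protocol article*

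**What the plan says.** All references are to the protocol article.

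- **Reporting route (Ethics).** "Parents are advised to immediately contact the chiropractor (who can contact the PI if relevant) if they suspect any serious adverse effect". No criterion for relevance is given.
- **Who receives the report (Randomization and blinding).** "Only the chiropractor has the list that reveals if that certain randomization number means allocation to intervention or control group". The same section says that "the intervention in this trial makes blinding of care providers impossible".
- **Who may not be told.** The PI is a physician (Visit 1: "the PI, who is a medical doctor, assesses the child for eligibility"). For the analyses, "the coding of intervention and control groups will be concealed from the PI and the statisticians performing the analyses".
- **Oversight (Ethics).** There are no interim analyses and no data monitoring committee. The regional ethics committee "reviews an annual safety report and any amendments made in the protocol". The source of the events in that report is not stated.
- **Other capture.** Ethics has every discontinuation registered with its reason. In Outcome measures, "Secondary outcomes are based on information from parental diaries and the final questionnaire filled out by the parents". That list names no adverse-event outcome, but it includes a General Perceived Effect scale with a category for increased colic, and regurgitation rated as more or less. The Intervention section names no side-effect item in the final questionnaire, but it does not claim to list every item.
- **Benefit and risk (Discussion).** After citing literature on the absence of reported serious side effects, the article concludes that "therefore a potential beneficial effect is likely to exceed potential risks".

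**The concern.** The article states the reporting rule, so this is not a gap in a condensed text. Three features of the rule matter together.

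1. The recipient delivered the treatment and knows the arm.
2. Passing the report on is permitted but not required.
3. The person who might not hear of it is the physician from whom the group coding is concealed, and who is therefore better placed to judge an event without knowledge of treatment.

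Such a filter can lose events. Because it works with knowledge of the arm, it can also lose them unequally. The same event could seem relevant in a manipulated infant and irrelevant in a control infant, or the reverse. A comparison of events by arm would then mix the effect of treatment with the effect of the reporting route. With no data monitoring committee, the annual safety report is the only periodic safety review described, so incomplete input would matter there too.

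**Working it through.** **Step 1. The plan's own figure.** The article gives no figure for harms. The only number needed is the arm size in Sample size: 100 per group, from a difference of 1 h, SD 2.5 h, significance level 0.05 (taken as two-sided) and power 80%.

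n per arm = 2 × (1.960 + 0.842)² × 2.5² / 1² ≈ 98.1, rounded up to 99, or 198 in total. The stated 200 reproduces, with power about 80.7% at 100 per arm. That figure is not in dispute.

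**Step 2. What each described source would capture.**

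| Source | Passes through the chiropractor's discretion? | What it misses |
|---|---|---|
| Parent contacts chiropractor, who may tell the PI | Yes | Events judged not relevant |
| Reasons for discontinuation | Not stated | Every family that stays in |
| General Perceived Effect, regurgitation and other questionnaire items | No, reported by blinded parents in both arms | Any event that is not a change in colic, bowel movements, burps or regurgitation |
| Diary of crying and sleep | No | Any event not expressed as crying, sleep, feeding or bowel pattern |

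For a serious event of another kind, in a family that remains in the trial, only the first row is designed to catch it.

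**Step 3. Illustration of lost events.** Let *f* be the share of events that is forwarded. The documents give no value for *f*, so all values below 1 are assumptions. With no events recorded among 100 treated infants, the one-sided 95% upper bound on the true rate is

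(1 − 0.05^(1/100)) / *f* = 0.0295 / *f*

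The chance that at least one event is recorded, at an assumed true rate of 3%, is 1 − (1 − 0.03*f*)^100.

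| *f* (assumed) | Upper bound with 0/100 | Chance of at least one recorded event at a true 3% |
|---|---|---|
| 1 | 2.95% | 95.2% |
| 0.5 | 5.9% | 77.9% |
| 0.25 | 11.8% | 52.9% |

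**Step 4. Illustration of unequal filtering.** If both arms have the same true rate, the expected ratio of recorded rates is *f* (treated) / *f* (control). With shares of 0.5 and 1 (assumed), it is 0.5 / 1 = 0.5. The treated arm would appear to have half the harm of the control arm when there is no difference. Reversing the shares gives 1 / 0.5 = 2. The direction cannot be known from the documents.

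**The case against.** The strongest reply is that one sentence of advice to parents is being read as a full reporting system. The article is condensed, and the parent information, the final questionnaire and the full protocol are not shown. The sentence does not set out the chiropractors' own duties, and its parenthesis could mean clinical escalation to a physician rather than data capture. Parents are advised, not restricted: they enrol by telephoning the PI and meet her at home twice, so they can reach her. Withdrawals are registered with reasons, and some worsening comes from blinded parents with no filter at all.

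Much of this stands, and it rules out several stronger readings that a reader might infer:

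- *That suspected harms reach nobody but the chiropractor.* Parents may contact the PI, and withdrawal reasons are a second, partial source.
- *That non-serious effects are barred from reporting.* The sentence concerns serious effects. It gives no route for others, but it excludes none, and the full protocol may cover them.
- *That the annual safety report contains only what chiropractors chose to pass on.* Its source is not stated, so incompleteness is possible but not shown.
- *That the benefit-risk statement in the Discussion rests on filtered events.* It rests on cited literature and uses no event from this trial, so it is not itself affected.

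It is also fair to say that sample size limits any safety conclusion. Even with complete forwarding, 0/100 leaves rates up to about 3% possible.

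The reply does not remove the wording itself. The article says who is told and makes the next step optional. If a fuller document requires forwarding, the article contradicts it and needs correcting.

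**Conclusion.** The point holds in a limited form. As written, the described route permits serious events in continuing families to go unrecorded, and to do so differently by arm, because an unblinded care provider decides what is passed on. A low or zero count from this trial could therefore not be taken as evidence of safety, and the annual safety report may be incomplete.

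The size is unknown. The move in the upper bound from 2.95% to 5.9% assumes that half of events are forwarded, and nothing in the documents supports that or any other share. No figure in the article is wrong on this point, and the primary crying analysis is not touched. This is a worthwhile, inexpensive correction to harm capture. It is not evidence that events have been withheld.

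**What to change.** - **Reporting rule.** Replace the parenthesis in the Ethics sentence with a requirement that chiropractors record every suspected adverse effect in both arms, serious or not, and forward it to the PI or the data manager without stating the arm.
- **Questionnaire.** If the final questionnaire has no item on suspected side effects, add one. The questionnaire is handed in before families are told the allocation, so the answer comes from blinded parents in both arms.
- **Use of the records.** Tabulate events by arm, together with the registered reasons for discontinuation, and state that the annual safety report draws on these records.

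The cost is one amended sentence, at most one questionnaire item and one table. More minor events will be logged. Recruitment is ongoing, so infants who have already completed the trial will lack the new item, and the table should show how many were asked. Families who discontinue are told their allocation, so their reports should go to someone other than the PI, such as the data manager, to avoid unblinding her.

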### Intervention

The study is pragmatic and assesses the effect of the treatment the clinician finds indicated, rather than a standard treatment. Therefore the study does not investigate a specific manual treatment, but investigates the whole chiropractic intervention with individual attention to the children’s potential biomechanical dysfunctions, as described below.

All children attend the chiropractor clinic two times a week for two weeks. After the fourth visit the parents continue their registration in the diary as an ‘after registration’ for at least three days, and fill out the final questionnaire including questions regarding the status of their child’s colic, bowel movements, burps, regurgitation and their belief regarding group allocation (Additional file 7). Hereafter an information visit takes place at the chiropractic clinic, where the parents hand in the completed diary and questionnaire and are informed whether their child has been in the treatment or control group. Children in the control group are then offered a similar treatment free of charge as the intervention group, if symptoms have not subsided, a strategy to improve adherence to the study.

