### Sample size

Based on data from the pilot study we observed a mean reduction in hours of crying in the control group of 2.5 h per day before and after treatment with a standard deviation of 2.5 h. Based on group discussions in the research group to obtain a clinically satisfactory result, we therefore wish that children in the intervention group will have a reduction of one additional hour, resulting in a reduction of 3.5 crying hours. With an assumption of a common standard deviation of 2.5, a level of significance on 0.05 and a power of 80%, this result in a sample size of 200 children distributed with 100 in each group.

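### The only stated adverse-effect route is parent-initiated and limited to suspected serious effects in the project period; no harm outcome or by-arm harm analysis is stated

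*Protocol article*

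**What the plan says.** **Reporting rule (Ethics).** Parents are advised to contact the treating chiropractor at once "if they suspect any serious adverse effect during the project period". The chiropractor may pass the report to the primary investigator if it is judged relevant. The same section says that withdrawals are registered with their reason, and that the ethics committee reviews an annual safety report. The content of that report is not described.

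**Outcomes and analyses (Outcome measures; Statistical analyses).** The primary outcome is change in crying hours. The secondary outcomes are sleep, contented waking time, general perceived effect, bowel movements, burps and regurgitation. No adverse-event outcome is listed and no comparison of harms between arms is described.

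**Final questionnaire (Intervention).** Its contents are described as including "questions regarding the status of their child’s colic, bowel movements, burps, regurgitation and their belief regarding group allocation". Parents complete it before they learn the allocation.

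**Later treatment of controls (Intervention).** The diary and questionnaire are handed in at the information visit and the allocation is revealed. "Children in the control group are then offered a similar treatment free of charge as the intervention group, if symptoms have not subsided". No data collection after this point is described.

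**Benefit and risk (Discussion).** The article observes that serious side effects of chiropractic care in infants have not been reported, "therefore a potential beneficial effect is likely to exceed potential risks".

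**The concern.** The point is what is collected and when.

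- **Threshold.** A report needs a parent to suspect an effect and also to judge it serious. Parents leave the room during treatment and do not know whether anything was done, so they have little basis for attributing an event to it.
- **Scope.** A non-serious reaction outside the listed symptoms, or an unplanned visit to a doctor, has no stated place to be recorded in either arm.
- **Window.** Control children with remaining symptoms are offered the treatment through the trial, but only after the last described data collection.

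A report of no harms could then reflect the collection rule as easily as the treatment. The trial has a concurrent control arm, blinded parents and a questionnaire completed before the reveal, which is a good setting for controlled harm data. As described, it would largely repeat the argument from absence of reports that the Discussion already makes.

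**Working it through.** **1. The article's own figure.** The only calculated figure is the sample size. Inputs from Sample size: difference 1 h ("will have a reduction of one additional hour"), SD 2.5 h ("With an assumption of a common standard deviation of 2.5"), and "a level of significance on 0.05 and a power of 80" percent. Allocation is 1:1 (Randomization and blinding). A two-sided test is assumed because sidedness is not stated.

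n per group = 2 × (1.960 + 0.842)² × 2.5² / 1² = 2 × 7.849 × 6.25 = 98.1, so 99 per group and 198 in total, against the stated 200. Power at 100 per group is 80.7% by the normal approximation and 80.4% by the noncentral t. The figure reproduces and is not disputed. It was set for crying time and carries no information about harms.

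**2. What each stated route can record.**

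| Route | Both arms before the reveal | Non-serious events | Symptoms outside the listed ones | Controls treated later |
|---|---|---|---|---|
| Parent contact (Ethics) | yes | no | only if judged serious | outside the implied window |
| Crying and sleep diary | yes | yes | no | no, already handed in |
| Bowel, burp, regurgitation and perceived-effect items | yes | yes | no | no, already handed in |
| Withdrawal with reason | yes | only if the family leaves | only if the family leaves | not described |
| Annual safety report | content not described | content not described | content not described | content not described |

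No row shows systematic collection of non-serious events outside the listed symptoms, and no row shows harm follow-up of controls treated later.

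**3. End of the project period.** It is not defined outright. Two statements imply it. Parents are blinded during that period, and blinding ends at the information visit. The diary is kept for the whole period and is handed in at that visit. The free treatment comes afterwards.

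**4. Size of the exposure outside the window.** Uptake among controls is not given. If all 100 accept, 100 of 200 treated infants (50%) fall outside. If half accept, 50 of 150 (33%) do. If none accept, the share is 0. The offer depends on symptoms persisting, so 100 is a ceiling.

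**5. What zero events would show (illustration, serious events, complete capture assumed).** The one-sided 95% upper limit for 0 of n is 1 − 0.05^(1/n). The upper end of the two-sided exact 95% interval is 1 − 0.025^(1/n).

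| Treated infants followed | One-sided limit | Two-sided upper end |
|---|---|---|
| 100 | 2.95% | 3.62% |
| 150 | 1.98% | not computed |
| 200 | 1.49% | 1.83% |

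At an assumed true rate of 1%, the chance of seeing at least one event is 1 − 0.99^100 = 63.4% with 100 infants and 1 − 0.99^200 = 86.6% with 200. These figures show how little an absence of serious events would establish. They do not measure how many milder reactions go unrecorded, and the article offers no basis for estimating that number.

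**The case against.** The strongest reply has four parts.

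**Several possible harms are measured in both arms.** A child can cry more, sleep less, regurgitate more, or have harder bowel movements or burps, and parents record this while blinded. The secondary outcomes are to be analysed like the primary. This stands. A reader might infer that no between-arm comparison of reactions is possible, and for these symptoms that is wrong. The gap is confined to reactions and medical contacts outside the list.

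**Other routes exist and the forms are not shown.** Withdrawal reasons carry no seriousness threshold, and there is a safety report. The questionnaire is an additional file that the article only summarises, and a condensed article can leave adverse-event detail to the full protocol. A reader might infer that milder reactions are never counted; the document cannot establish that. But the reporting threshold is printed, not merely omitted, and the outcome list that is printed contains no adverse-event outcome.

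**The article claims less than it may seem to.** A reader might infer that it concludes from its own data that benefit exceeds risk. The Discussion sentence speaks of a potential benefit, relies on cited literature and reports no trial result. A reader might also infer that the absence of reported effects is why there is no monitoring committee. The reason given in Ethics is that the treatments are those of usual practice.

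**Later treatment of controls lies outside the randomised comparison.** That is so, and data from it would be uncontrolled. It is still exposure provided through the trial, and it can be reported separately as such.

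**Conclusion.** The concern holds in limited form. The one adverse-effect route the article states depends on blinded parents suspecting a serious effect within the project period. No adverse-event outcome or by-arm harm analysis is stated. Non-serious reactions outside the measured symptoms, and unplanned medical contacts, have no stated systematic collection, and no harm follow-up is described for controls treated after the reveal. The described data therefore could not test the benefit-risk argument in the Discussion.

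The number of unrecorded milder reactions cannot be estimated. The exposure outside the window ranges from 0 to 100 treatment courses, depending on uptake that is not given. This reading assumes that the project period ends at the information visit, and that the files not shown contain no harm item; if the final questionnaire already has one, what remains is to list and analyse it as an outcome. The primary analysis and the sample size are unaffected. This is an inexpensive improvement to harm data collection.

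**What to change.** 1. Add one solicited item to the existing final questionnaire, completed by both arms before the reveal: any new or worse symptom and any unplanned medical contact since the first clinic visit, with date and free text. Ask for no judgement of seriousness or cause. List it as a safety outcome and tabulate it by arm.
2. Extend the same item and the reporting advice to control children during the free treatment that follows the reveal. Report them separately as uncontrolled exposure, with the number who accepted.
3. In the results report, base any benefit-risk statement on these counts with confidence limits, and give the number of families who were asked.

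**Cost.** An ethics amendment, one table, and one more short form for control families who accept the later treatment. Children enrolled before the change will lack the item, so denominators will be smaller than 100 per arm. Both arms receive the item from the same date, so the by-arm comparison among later participants remains fair. Recruitment was ongoing when the article appeared, and the trial had already obtained approval for amendments after its pilot.
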